### Recruitment {15}

Caregivers of children selected for ORL surgery and accessing the hospital are screened according to inclusion and exclusion criteria. The caregivers are offered to participate in this study. Recruitment is expected to last 8 months and will continue until the estimated sample size is reached.

### Assignment of interventions: allocation

#### Sequence generation {16a}

Enrolled caregivers are randomly assigned into two groups (experimental group A and control group B) using a computerised number generation with simple randomisation and block randomisation with a block size of four to ensure a good balance of participants between the two groups.

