### Trial design {8}

A two-parallel arm, open randomised controlled trial is being conducted to evaluate the superiority of an mHealth app in reducing anxiety in caregivers of children undergoing tonsillectomy and/or adenoidectomy with or without insertion of a tympanostomy tube in the perioperative period compared to standard care. Standard care in the control group consists of information and education provided by nurses and physicians during preoperative visits and hospitalisation about the ORL perioperative process. The information and education are provided orally or through printed brochures. Eligible participants are randomly allocated in a 1:1 ratio to the intervention group (use of mHealth app) or the control group (standard care).

Our study protocol followed the SPIRIT guidelines [16].

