## Methods: participants, interventions, and outcomes

### Study setting {9}

The study is monocentric and is being conducted in a 136-bed maternal and child health hospital in Northern Italy. In this hospital, a number of approximately 450 tonsillectomies or adeno-tonsillectomies are performed each year. Specifically, enrolment started December 16, 2022, and is taking place in the consulting rooms of the paediatric surgery ORL department. Data collection is being performed in the paediatric surgery ward and in the ORL department. Statistical data analysis will be held at the clinical epidemiology and public health research unit of the same hospital.

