### Who will take informed consent? {26a}

Nursing staff in the consultation rooms of the paediatric surgery ORL department are in charge of informing eligible caregivers about the study and obtaining signed informed consent from caregivers to voluntarily participate in the study.

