#### Concealment mechanism {16b}

The allocation process is undertaken by the hospital’s Clinical Epidemiology and Public Health Research Unit to ensure random allocation and concealment. The allocation sequence is hidden from the researchers and other staff involved in the study in sealed, opaque, sequentially numbered envelopes.

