#### Implementation {16c}

The nurse in the consultation rooms of the ORL paediatric surgery department is in charge to open the envelopes and give access to the app to group A, according to the number extracted and corresponding to the study arm.

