### Assignment of interventions: blinding

#### Who will be blinded {17a}

Healthcare providers and participants could not be blinded in this study because the app in use is visible to caregivers and staff. Outcome assessors could not be blinded in this study.

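### The article names two incompatible randomisation schemes; on the only reading that fits, a fixed block of four at one open-label site would let a fully informed observer foresee up to a third of allocations

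*Protocol article*

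**What the plan says.** All references are to the protocol article.

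- **Sequence generation {16a}:** caregivers are assigned "using a computerised number generation with simple randomisation and block randomisation with a block size of four to ensure a good balance". One block size is given. No variation in size and no stratification are described.
- **Trial design {8}:** "Eligible participants are randomly allocated in a 1:1 ratio to the intervention group".
- **Study setting {9}:** "The study is monocentric and is being conducted in a 136-bed maternal and child health hospital in Northern Italy".
- **Who will be blinded {17a}:** the article states: "Healthcare providers and participants could not be blinded in this study because the app in use is visible to caregivers and staff".
- **Who will take informed consent? {26a}:** nursing staff of the ORL consultation rooms inform eligible caregivers and are responsible for "obtaining signed informed consent from caregivers to voluntarily participate in the study".
- **Intervention description {11a}:** nurses of the department enrol caregivers and instruct group A on the app.
- **Implementation {16c}:** the nurse in those rooms "is in charge to open the envelopes and give access to the app to group A".
- **Concealment mechanism {16b}:** the hospital's clinical epidemiology unit runs the allocation "to ensure random allocation and concealment", and opaque, sealed, consecutively numbered envelopes hide the sequence from researchers and staff.
- **Participant timeline {13}:** T0, which includes baseline state and trait anxiety, takes place once the caregiver has been enrolled and allocated.

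**The concern.** There are two problems, and the second depends on how the first is resolved.

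First, simple randomisation draws each assignment independently, while blocking forces equal numbers within each block. One list cannot do both, so a reader cannot tell how participants were allocated.

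Second, if blocks of four were used, each block must contain two of each arm. In an open trial the opened envelopes are informative about the next one. Opaque envelopes stop anyone reading the next card, but they do not stop anyone working it out. The nursing staff who speak to families before consent belong to the same consultation rooms as the nurse who opens the envelopes.

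Staff who could foresee the next arm could, even unintentionally, influence whom they approach or when. Analysing by intention to treat and comparing arms with a Wilcoxon or t-test does not correct for selective enrolment, because the groups would differ before treatment starts. The primary outcome is the caregiver's self-reported anxiety, which plausibly varies with who is approached.

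**Working it through.** **The plan's own figure.** The article gives no figure for predictability. Its only related number is the sample size (Sample size {14}). Pooled SD = √((13² + 10²)/2) = 11.60, and d = 5/11.60 = 0.43. A two-sided Wilcoxon-Mann-Whitney test at alpha 0.05 (relative efficiency 3/π) needs 90 per arm for 80% power. The stated 180 is reproduced, and it equals 180/4 = 45 whole blocks.

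**Inputs.** Block size 4 ({16a}); ratio 1:1, so two A and two B per block ({8}); total 180 ({14}). Assumption: the observer knows the block size and has seen all earlier allocations in order.

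**Allocations known with certainty.** An assignment is certain once one arm's two places in the block are used. The six possible blocks are:

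| Block | Certain positions |
|---|---|
| AABB | 3rd and 4th |
| BBAA | 3rd and 4th |
| ABAB | 4th |
| ABBA | 4th |
| BAAB | 4th |
| BABA | 4th |

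The total is 2 + 2 + 1 + 1 + 1 + 1 = 8 of 6 × 4 = 24 positions, or 33.3%. Over the trial that is 180 × 8/24 = 60.

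**Best guess.** Always guess the arm that is behind in the block, and toss a coin when they are level.

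- 1st position: 1/2
- 2nd position: 2/3
- 3rd position: (1/3 × 1) + (2/3 × 1/2) = 2/3
- 4th position: 1

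The average is (1/2 + 2/3 + 2/3 + 1)/4 = 17/24 = 70.8%, or 127.5 of 180.

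**Alternatives.** The varying-size rows come from simulation of lists of 180. The observer knows the set of sizes and the full history, but not which size was drawn.

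| Scheme | Known with certainty | Best guess correct |
|---|---|---|
| Fixed 4 | 33.3% | 70.8% |
| Random 4/6 | 5.5% | 69.2% |
| Random 4/6/8 | 2.3% | 68.0% |
| Simple | 0% | 50% |

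For 4/6/8, 2.3% of 180 is about 4 participants. Including blocks of two does not help: 2/4/6/8 gives 68.7% correct guesses.

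**Is there room for selection?** Study setting {9} gives about 450 tonsillectomies or adeno-tonsillectomies a year. At a steady rate, 8 months (Recruitment {15}) gives 450 × 8/12 = 300, of which 180 is 60%. One year (Trial status) gives 180/450 = 40%. This ignores ineligible and declining families, and adenoidectomy-only cases, which would add to the pool. It shows only that not every family needs to be enrolled.

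**The case against.** The strongest reply is that one third describes an ideal observer. That person must know the block size, know where each block starts and have seen the whole run. The article says none of this about the nurses. It describes a separate unit that runs the allocation and a sequence hidden from staff, and it does not say how many nurses share the work. Printing the block size in an article does not show that clinic staff read it. All of this stands. A reader might infer that a third of allocations actually were foreseen, that concealment failed or that the result is biased. The document supports none of these. It makes inference possible, and it describes no safeguard beyond the envelopes.

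It can also be said that the two-scheme wording is a slip, since the block size and the purpose in the same sentence point to blocks. That is probably right, and it makes the wording a short edit. It also makes the fixed block size the operative design.

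Third, varying the block size hardly changes best-guess success. This stands as well: the gain lies in removing near-certain knowledge, not in making guessing useless.

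Finally, baseline anxiety is collected, so gross selection could be looked for. This holds only in part. T0 follows allocation, so a baseline difference could reflect selective enrolment or a reaction to learning the arm. The consecutive numbering of the envelopes already implies use in order, so that part of the fix only makes it explicit.

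**Conclusion.** The point holds in a conditional form. The description of the sequence contradicts itself and should name one method; only blocking fits the stated aim. Under blocking, the design allows up to one third of allocations (60 of 180) to be known with certainty, and about 71% to be guessed correctly. These figures assume a single fixed block of four, no strata, and an observer who knows the block size and has followed every allocation. If the list was in fact simple randomisation, no allocation is predictable.

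No bias is shown, and its direction and size on the anxiety score cannot be estimated from the article. The sample size is unaffected. This is an inexpensive improvement to make, not a defect that invalidates the trial.

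**What to change.** 1. In Sequence generation {16a}, delete the reference to simple randomisation and state one scheme.
2. For envelopes not yet opened, have the clinical epidemiology unit issue a new list in permuted blocks of randomly varying size, for example 4, 6 and 8, and withhold the sizes from enrolling staff.
3. State in Implementation {16c} that each envelope is opened in number order, only after consent is signed and the T0 measures are complete. Amend Participant timeline {13} so that T0 precedes allocation.
4. If enrolment is already complete, which is possible given the estimated study end of 31 December 2023, report the method actually used and whether enrolling staff knew the block size.

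**Cost.** One new list and a new set of envelopes are needed. So is an amendment, with ethics approval and a registry update if it is judged important under Plans for communicating important protocol amendments {25}. A small final imbalance is possible: an unfinished block of 8 leaves at most 4, and abandoning a current block of 4 leaves at most 2, so at most 4 + 2 = 6 participants. Steps 2 and 3 affect only participants not yet randomised, and the article does not give their number.

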#### Concealment mechanism {16b}

The allocation process is undertaken by the hospital’s Clinical Epidemiology and Public Health Research Unit to ensure random allocation and concealment. The allocation sequence is hidden from the researchers and other staff involved in the study in sealed, opaque, sequentially numbered envelopes.

#### Implementation {16c}

The nurse in the consultation rooms of the ORL paediatric surgery department is in charge to open the envelopes and give access to the app to group A, according to the number extracted and corresponding to the study arm.

### Assignment of interventions: blinding

#### Who will be blinded {17a}

Healthcare providers and participants could not be blinded in this study because the app in use is visible to caregivers and staff. Outcome assessors could not be blinded in this study.

#### Procedure for unblinding if needed {17b}

Because this study is an open-label study, no unblinding procedures are used.


Caregivers are asked to complete both forms at T0 to determine anxiety trait and baseline levels. The state form of the STAI Form Y-1 is completed in the hospital surgical department prior to surgery at T2 and again on the seventh day after surgery (follow-up) at T3 to measure study outcomes**.**The modified Yale Preoperative Anxiety Scale (mYPAS) [22] is used as an observational tool to measure anxiety in children in the preoperative period at T2. The mYPAS consists of 27 items that examine five domains, such as child activity, emotional expressiveness, arousal state, vocalisation, and caregiver engagement. Scores range from 23.33 to 100, with higher scores indicating higher levels of anxiety. The tool is completed by nurses. Since there is no validated Italian version of the questionnaire, only English-speaking nurses are responsible for completing the instrument, according to Liguori and colleagues [24].The social and health impact of the study is self-assessed by caregivers at follow-up (T3) through outcome measures, such as how often caregivers had to call the hospital for additional information, had to visit the paediatric Emergency department, or had other complications at home after surgery (e.g. bleeding, uncontrolled pain).

The questionnaires at T0 and T2 are completed online via a tablet available to participants in groups A and B and to nurses in the surgical department. The assessment at T1 is completed in paper form. Moreover, considering that in this hospital not all caregivers bring their child for follow-up, sometimes preferring to see their general paediatrician, data collection at T3 is performed online after sending caregivers an email with a link to fill out the questionnaires.

Prior to the start of the study, nurses in the surgical department participating in the study were trained in the use of the assessment tools (e.g. mYPAS) with standardised instructions. The training was conducted by a nurse from the research ream in a meeting room of the department.

#### Other assessments (only group A)

Data on app usage (number of logins; quality of content consulted, time spent on app) will be collected during experimentation of the app.At the end of the trial, participants are asked to provide an evaluation over the app’s content and features in digital form through the app itself.

### Plans to promote participant retention and complete follow-up {18b}

Data collection is conducted during the perioperative period when caregivers are in the hospital for visits and surgery, so participant presence in the hospital of participants eases data collection. As with any ORL surgical process at this hospital, participants in groups A and B are encouraged to attend the scheduled follow-up visit and are reminded by email to complete the questionnaires for the final assessments on T3, the day of follow-up.

### Data management {19}

Most data are collected electronically through an interface that complies with European (GDPR No. 679/2016) and Italian (D.L. 101/2018) data protection guidelines. Participants are pseudo-anonymised and given a ID number. Data collected at T1 on a paper form will be entered into an electronic record protected by a password. Two nurses will enter the data collected at T1 to verify correct entry. The data will be processed by the Clinical Epidemiology and Public Health Research Unit of the hospital using the SAS software, Version 9.4 (SAS Institute Inc., Cary, NC, USA) for data analysis. Access to the data will be restricted, and researchers and statisticians will be assigned a user ID and password.

### Confidentiality {27}

Confidentiality is ensured by assigning a unique participant code number to each participant to ensure pseudo-anonymisation. Confidentiality and anonymity of study participants are ensured according to European (GDPR No. 679/2016) and Italian (D.L. 101/2018) regulations.

### Plans for collection, laboratory evaluation, and storage of biological specimens for genetic or molecular analysis in this trial/future use {33}

No biological specimens will be collected.

## Statistical methods

### Statistical methods for primary and secondary outcomes {20a}

Description of the categorical variables will be made using frequency and percentage while mean and standard deviation (or median and interquartile range if variables are not normal) will be reported for continuous variables. Data will be analysed by intention-to-treat. A per-protocol analysis will be also performed. To evaluate the difference in the score of preoperative anxiety between intervention and control group, Wilcoxon-Mann–Whitney non-parametric test (or *t*-test, as necessary) will be applied. The same test will be calculated to evaluate the difference in the anxiety score between intervention and control group at T0 and T3.

Wilcoxon-Mann–Whitney will be also used to establish if a difference in the children distress will be between intervention and control group. Chi-square test or exact Fisher test will be applied to evaluate difference in the family preparation for hospitalisation and surgery at T1 between group A and B.

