### Sample size {14}

Assuming a mean score of preoperative anxiety (main outcome of the study) of 50 for the control group, with a standard deviation (SD) of 13 [21], and a mean of 45 for the intervention group, with SD of 10 (effect size = 0.43), an alpha value of 0.05 and a beta value of 0.20, 180 subjects (90 per group) are needed to conduct the study (G*power, Wilcoxon-Mann–Whitney test, two groups).

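### The primary test is valid but unadjusted, leaves open a switch to a t-test, and makes no use of T0 anxiety; a pre-specified ANCOVA is a cheap gain if the covariate is not affected by allocation

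*Protocol article*

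**What the plan says.** All references are to the protocol article.

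- **Primary test.** Statistical methods {20a}: "To evaluate the difference in the score of preoperative anxiety between intervention and control group, Wilcoxon-Mann–Whitney non-parametric test". A parenthesis allows a t-test instead where necessary, without saying what makes it necessary. No covariate is named.
- **Baseline anxiety.** Assessment tools: "Caregivers are asked to complete both forms at T0 to determine anxiety trait and baseline levels". This covers STAI-Y1 (state) and STAI-Y2 (trait) in both arms.
- **Use of that baseline.** {20a}: "The same test will be calculated to evaluate the difference in the anxiety score between intervention and control group at T0 and T3". Section {20b} plans no additional analyses.
- **Timing of T0.** Participant timeline {13} places T0 after enrolment and allocation. Section {17a} says that participants, providers and outcome assessors are not blinded.
- **Sample size {14}.** "180 subjects (90 per group) are needed to conduct the study", computed for the Wilcoxon-Mann–Whitney test with no term for loss. The abstract enrols the same 180, and Recruitment {15} ends when the estimated size is reached.
- **Missing data {20c}.** The main analysis covers randomised subjects with an available main outcome. Reasons for dropout are recorded, and multiple imputation is named. No dropout rate is given.

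**The concern.** State anxiety a week earlier and trait anxiety are natural predictors of state anxiety before theatre. If they are, a comparison that leaves them out has a wider interval than it needs and leaves chance imbalance in baseline anxiety uncorrected. Testing T0 between randomised arms does not help: it removes no imbalance and adds no precision.

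The unruled switch between two tests leaves a choice that could be made after the data are seen. The two tests address different hypotheses, and a Wilcoxon p-value does not itself estimate the between-group difference that Outcomes {12} names as the primary outcome.

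The sample size leaves no margin for missing T2 scores, so unused precision matters more here than it would in a generously sized trial.

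**Working it through.** **Inputs from the protocol.** Control mean "of 50 for the control group, with a standard deviation (SD) of 13"; intervention mean 45 with SD 10; "an alpha value of 0.05 and a beta value of 0.20"; 90 per group; 1:1 allocation. Sidedness is not stated.

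**Inputs assumed.** Correlation r between the T0 covariate and T2 state anxiety, 0.3 to 0.6. Loss of T2 scores, 5% and 10%. The documents give neither.

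**1. Reproduce the 180.**
- Common SD = √((13² + 10²)/2) = √134.5 = 11.60; d = 5/11.60 = 0.431, matching the stated 0.43.
- A two-sided t-test at 80% power needs 85.4 per arm (85.9 with d = 0.43).
- Dividing by the Wilcoxon efficiency for normal data, 3/π = 0.955, gives 89.5 (89.9), hence 90 per arm and 180 in total. The figure reproduces.
- A one-sided calculation gives 67 per arm before the efficiency correction and does not reproduce it.

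**2. Power of the planned test** (noncentral t, effective n = 0.955 × n per arm).

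| T2 loss (assumed) | n per arm | Wilcoxon | t-test |
|---|---|---|---|
| 0% | 90 | 80.2% | 82.0% |
| 5% | 85.5 | 78.2% | 80.0% |
| 10% | 81 | 75.9% | 77.9% |

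A simulation of 20,000 trials with means 50 and 45 and SDs 13 and 10 gave 79.8% for Wilcoxon at 90 per arm.

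**3. Power with adjustment.** The residual SD is 11.60 × √(1 − r²), so the effective effect size is 0.431/√(1 − r²).

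| r (assumed) | effect size | 90 per arm | 81 per arm (10% loss) |
|---|---|---|---|
| 0.3 | 0.452 | 85.4% | 81.6% |
| 0.4 | 0.470 | 88.1% | 84.5% |
| 0.5 | 0.498 | 91.3% | 88.3% |
| 0.6 | 0.539 | 94.9% | 92.6% |

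A weaker covariate gains less: r = 0.2 gives 0.431/√0.96 = 0.440 and 83.5% at 90 per arm. About 1.8 points of any gain over Wilcoxon (82.0 − 80.2) comes from analysing means rather than ranks, not from the covariate.

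**4. What happens if T0 state anxiety already reflects the arm.** Suppose that knowing the allocation lowers T0 state anxiety by 2 points in the app arm (assumed) while the true T2 difference stays at 5. With equal SDs at T0 and T2, ANCOVA estimates 5 − 2r.

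| r | estimate | power at 90 per arm |
|---|---|---|
| 0.4 | 4.2 | about 75% |
| 0.5 | 4.0 | about 76% |
| 0.6 | 3.8 | about 78% |

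These fall below the 80.2% of the unadjusted test. With a 1-point shift, power at the same correlations is about 82%, 85% and 89%. The documents give no evidence of any shift; the calculation shows only why the timing matters.

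**The case against.** **The planned test is valid.** Randomisation protects an unadjusted comparison. A reader might infer that the primary analysis is biased or wrong; nothing in the protocol supports that. This objection stands, and the point is one of efficiency and pre-specification.

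**Adjusting for T0 state anxiety could do harm.** As written, T0 follows allocation and nobody is blinded, so a scale that asks how the caregiver feels now may already carry an effect of the arm. A reader might infer that an ANCOVA on T0 state simply restores power at no risk; step 4 of the working shows that it need not. This also stands and changes the remedy. Trait anxiety, which asks how the caregiver feels in general, is less exposed.

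**The loss argument is easily overstated.** A reader might infer that the trial expects dropouts and is therefore underpowered. Section {20c} only says that reasons are recorded, and it names multiple imputation. T2 is taken in hospital before theatre, about seven days after enrolment, so loss may be small; T3, completed online, is more exposed but is secondary. What remains is that 180 carries no margin for the Wilcoxon test.

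**Wilcoxon is the evident default.** It is named first and was used for sizing, so it goes too far to say that the primary p-value is undetermined. The absence of a rule for the switch remains. The form of the effect estimate is often left to an analysis plan, which is not shown, so its absence is not counted as a fault.

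**Conclusion.** The point holds as a cheap improvement, not as the correction of an error. The protocol itself fixes an unadjusted primary test with an unruled alternative and makes no use, beyond a T0 significance test, of anxiety data that it already collects.

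At 90 per arm, adjustment would raise power from 80.2% to about 85–95% for assumed correlations of 0.3 to 0.6. The gain is smaller if trait anxiety alone is used and correlates less with T2 state anxiety. The range rests on an approximately linear relation, on the protocol's means and SDs, and on a covariate unaffected by allocation. That last condition is not secured by the timeline as written.

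The stated 80% power for the Wilcoxon test holds only with complete T2 scores. How far actual power would fall cannot be known from the documents.

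**What to change.** 1. In {20a}, name one primary analysis: an ANCOVA of T2 STAI-Y1 on arm and T0 anxiety, with robust standard errors because the assumed SDs differ (13 and 10). Report the adjusted mean difference with its 95% CI. Keep Wilcoxon as a sensitivity analysis and remove the open switch to a t-test.
2. Use the same model at T3, and drop the T0 significance test.
3. In {13}, have T0 completed before the envelope is opened. For caregivers already enrolled with T0 after allocation, use T0 trait anxiety (STAI-Y2) as the primary covariate and move adjustment for T0 state anxiety to a sensitivity analysis. One model needs the same covariate for everyone, so if such caregivers are in the analysis set, trait is the primary covariate throughout.
4. In {14}, state that 180 gives 80% power for the Wilcoxon test only with no missing T2 scores, with about 78% at an assumed 5% loss and 76% at 10%.

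**Cost.** No new data and no more families. The changes are analysis wording plus, for future enrolees, a change in the order of T0 and envelope opening. The analysis then relies on a linear adjustment, with Wilcoxon as a check. The model should be fixed before outcome data are analysed.
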